#### Development safety update reports

In addition to the expedited reporting above, the Chief Investigator shall submit once a year throughout the clinical trial on the anniversary of the clinical trial authorization CTAor on request a development update safety report (DSUR) to the competent authorities (MHRA in the UK), research ethics committee concerned, host NHS Trust and Sponsor.

### Statistics

#### Statistical analysis for effectiveness and safety

The primary analysis will be intention-to-treat assuming no resolution for missing data. The proportion of complete resolution at 24 hours reported by participants will be compared between two treatment arms using a generalized linear regression model for binary data adjusting for whether participants are prescribed antibiotics or not. The proportion of complete resolution at 24 hours in those participants who have not been prescribed antibiotics (on which this trial is powered) will be compared in the same way.

Logistic regression adjusting for whether participants are prescribed antibiotics or not will also be performed to estimate the differences in the proportions of binary secondary outcomes including reported complete resolution at 48 hours, hospital admission within 28 days, attendance at GP practice, Emergency Departments, or out-of-hours centers within 28 days with symptoms or complications associated with sore throat and uptake of delayed antibiotic prescription within seven days. We will explore whether positive bacterial throat swab, FeverPAIN score, Centor score and other baseline factors predict response to corticosteroid. Use of over-the-counter and prescribed medicine other than antibiotics will be summarized and compared using chi-square tests.

Mean and standard deviations for reported time to onset of pain relief, time to complete resolution of pain, duration of moderately bad symptoms recorded by validated symptom diary and time missed from work or education over the seven days from treatment onset will be calculated and compared between two treatment arms using a linear regression adjusting for antibiotic prescription. We will use data from participants’ diary on throat pain, pain on swallowing and difficulty in swallowing by visual analogue scale within seven days post-randomization to calculate areas under the curves as proxies for a summary measurement and tested for a difference between two arms using a linear regression adjusted for antibiotics prescription. All model assumptions will be assessed and if data do not conform to assumptions the alternatives will be explored. Symptoms of interest will be summarized in the proportions and difference between two treatment arms and 95% CI will be calculated. Full description of the methods to be used will be stated in a trial statistical analysis plan.

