Socio-demographic factors which will include: age, gender, smoking history and paid work or education. Medications which will include: decision whether or not to offer delayed antibiotic script and if offered, type of dose, dosing regimen and duration of antibiotics prescribed as well as whether the practice left the script for collection at reception or gave it to the patient at the baseline recruitment meeting and any other advised treatment. Symptoms which will include: the duration of sore throat and painful swallowing and the presence or absence of cough, hoarse voice, coryza and fever in last 24 hours, all of which use a validated scale, where ‘None’ is equal to absence of and ‘Slight’ ‘Moderate’ and ‘Severe’ are equal to presence of. Clinical examination findings which will include the confirmation of: the presence of pharyngeal inflammation, the presence of tonsils, the presence of inflamed tonsils, the presence of purulent tonsils, the presence of cervical lymphadenopathy, the presence of tender cervical lymphadenopathy, the participants temperature and type of thermometer used for measuring. Patient-completed items which will include: ratings of throat soreness, pain on swallowing and difficulty swallowing using visual analogue scales, baseline severity ratings using symptom diary and completion of the EuroQol EQ-5D-5L instrument [20].

All these procedures happen according to the schedule of procedures; see Additional file 2.

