#### The number of participants

Based on the results of our systematic review of eight studies, the average absolute increase in participants reporting complete resolution of pain at 24 hours with corticosteroids in addition to antibiotics and analgesia was 27% [15]. The minimum absolute increase from individual trials was 18% (11 versus 29%). To achieve this effect size with 90% power, our conservative estimate of sample size is 226 patients.

In the UK antibiotics are prescribed to approximately 50% of participants presenting with sore throat [1]. Given that our first secondary objective is to detect a clinically significant difference in proportions of participants not having been prescribed antibiotics, we will require an initial sample of 452 patients. A sample size of 566 allows for loss of up to 20% to follow-up (or 532 for 15% lost to follow-up).

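### A cheap improvement, not an error: the no-antibiotic comparison is in effect unadjusted, although throat soreness and symptom duration are recorded at baseline

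*Protocol article*

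**What the plan says.** Under Statistical analysis for effectiveness and safety, the article compares the primary outcome between arms "using a generalized linear regression model for binary data adjusting for whether participants are prescribed antibiotics or not". No other covariate is named. The proportion resolved "in those participants who have not been prescribed antibiotics (on which this trial is powered) will be compared in the same way". Prescription status is also the only adjustment named for the binary and continuous secondary outcomes. Other baseline factors appear in that section only as possible predictors of response to corticosteroid, not as covariates for the treatment comparison.

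Under Baseline assessments, the recorded items include "the duration of sore throat and painful swallowing" and "ratings of throat soreness, pain on swallowing and difficulty swallowing using visual analogue scales".

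Under Randomization and codebreaking, allocation is stratified by centre and by delayed prescription. Only the second factor enters the model.

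Under The number of participants, the design contrast is 11% versus 29%, and "To achieve this effect size with 90% power, our conservative estimate of sample size is 226 patients". About half of patients are expected to be prescribed antibiotics, so the 226 is doubled to 452 and then raised for loss to follow-up.

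**The concern.** The primary outcome is an absolute state one day after dosing, and patients may enter at any point in the first seven days of a self-limiting illness. How sore the throat is at entry, and how long it has been sore, could plausibly predict who is symptom-free a day later. If they do, leaving them out costs some power and leaves chance imbalance in severity uncorrected in the point estimate.

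The cost would fall mainly on the no-antibiotic comparison. It has half the patients, it determines the sample size, and its one named covariate takes a single value. At 11%, only about 12 placebo successes are expected among 113 (0.11 × 113 = 12.4).

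**Working it through.** **Inputs from the article.** Rates 11% and 29%; power 90%; 226 participants for the no-antibiotic comparison; 452 overall; 566 or 532 after 20% or 15% loss; 1:1 allocation; missing outcomes counted as not resolved.

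**Assumptions.** Two-sided 5% (the article states no alpha). Prognostic strength of the baseline values is not given, so a range is used.

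**1. Reproduce the plan's sample size.** With p̄ = 0.20 and Δ = 0.18:

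- Uncorrected n per arm = [1.96√(2 × 0.20 × 0.80) + 1.2816√(0.11 × 0.89 + 0.29 × 0.71)]² / 0.18² = 101.7, so 102 per arm (204).
- With continuity correction: (101.7/4) × [1 + √(1 + 4/(101.7 × 0.18))]² = 112.5, so 113 per arm. This matches the stated 226.
- 226/0.5 = 452; 452/0.8 = 565 (566 as two equal arms); 452/0.85 = 531.8, so 532.

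**2. Power of the planned analysis.** Power = Φ{[Δ√n − 1.96√(2p̄(1 − p̄))] / √(p₁q₁ + p₂q₂)}.

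- No-antibiotic, n = 113: (0.18 × 10.63 − 1.109)/0.551 = 1.46, giving 92.8%. It exceeds 90% because 226 includes the continuity correction.
- All participants, n = 226: (0.18 × 15.03 − 1.109)/0.551 = 2.90, giving 99.8%.
- No-antibiotic with 20% missing counted as not resolved: rates become 0.8 × 11% = 8.8% and 0.8 × 29% = 23.2%, with 566/4 = 141.5 per arm, giving 91.5%.

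**3. Approximate gain from adjustment.** If baseline covariates explain a share R² of outcome variance, replace n by n/(1 − R²). For example, R² = 0.10 gives 113/0.90 = 125.6 and power 95.0%.

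| Comparison | R² = 0 | 0.02 | 0.05 | 0.10 | 0.15 |
|---|---|---|---|---|---|
| No-antibiotic, 11% vs 29%, 113 per arm | 92.8% | 93.3% | 93.9% | 95.0% | 96.0% |
| Same, 20% missing as not resolved | 91.5% | 92.0% | 92.8% | 94.0% | 95.1% |
| No-antibiotic, 11% vs 23% | 67.3% | 68.1% | 69.5% | 71.9% | 74.3% |
| All participants, 11% vs 23%, 226 per arm | 92.7% | 93.2% | 93.9% | 95.0% | 96.0% |

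For all participants at 11% versus 29%, power stays between 99.8% and just under 100% throughout.

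**4. Check by simulation** (logistic model, Wald test, with and without covariates).

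- One standard-normal score, log odds ratio 0.5 to 1.2 per SD, 113 per arm: at 11% versus 29%, about 93% rises to 94–96%; at 11% versus 22%, about 60% rises to roughly 62–68%. All participants at the planned effect: about 99.9% either way.
- Two independent covariates, odds ratio 1.25, 1.5 or 2.0 per SD each, 113 per arm: at 11% versus 29%, 92.9% to 93.0%, 93.1% to 93.5%, and 93.0% to 95.6%; at 11% versus 23%, 67.0% to 67.6%, 67.8% to 70.7%, and 67.9% to 73.6%.
- With no prognostic value (odds ratio 1), the adjusted and unadjusted results differ by less than one point, within simulation error.

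**The case against.** The strongest reply is that nothing here is wrong. The model adjusts for a stratification factor in a randomised comparison, it is unbiased, and chance imbalance is already reflected in the confidence interval. This stands.

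A reader might infer that the primary analysis loses meaningful power, or that the trial is underpowered as planned. The documents do not support either reading. The primary comparison uses all participants and has about 99.8% power at the design effect. The no-antibiotic comparison is a secondary outcome and stays above 90%, even with 20% counted as not resolved.

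The larger gains need two assumptions together: a true effect below the 18 points that the article calls the smallest in any individual trial, and a strongly prognostic score. The article gives no prognostic strength, and a log odds ratio of 1.2 is an odds ratio of about 3.3 per SD. This also stands. A smaller effect is nevertheless conceivable, because the 18 points come from trials that gave steroids alongside antibiotics, only one of them in primary care.

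The article also defers full methods to an analysis plan that is not shown, and that plan may add covariates. This weakens the point but does not remove it. The article names a specific adjustment set and repeats it across outcomes, so a richer set in the analysis plan would differ from the published text and the two should be aligned.

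**Conclusion.** The point holds as a low-cost efficiency improvement. The one named covariate does nothing in the comparison on which the trial is sized, while two plausible predictors are already collected at baseline.

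The gain is conditional on those predictors being prognostic. For an assumed log odds ratio of 0.5 to 1.2 per SD for a single score, it is about 0 to 3 points in the no-antibiotic comparison at 113 per arm and 11% versus 29%, and about 2 to 8 points at 11% versus 22%. It is practically nil for the overall primary comparison at the planned effect, and nil everywhere if the baseline values are not prognostic.

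That the plan meets 90% power rests on a two-sided 5% test and on half of participants having no prescription. With a 40% share of 452, there would be 90.4 per arm and unadjusted power would be 86.3%, which is one more reason to use the available information.

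**What to change.** Before unblinding, state in the analysis plan that the 24-hour model for all participants, the no-antibiotic model and the 48-hour model include baseline throat-soreness score (continuous), duration of sore throat at entry, and centre as the other stratification factor. Retain prescription status wherever it varies.

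Fit a logistic model and report the risk difference and risk ratio standardised over the analysed sample, so that the reported effect stays marginal. The article names no link for the primary model. Continuous covariates can cause convergence failure with a log or identity link, and they change the meaning of a conditional odds ratio. Keep the prescription-only model as a sensitivity analysis.

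The cost is a slightly larger model, a simple rule for missing baseline values, and a short paragraph specifying the standardisation and its variance. No new data are needed.

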## Methods/Design

### Objectives

The primary objective of the trial is to investigate if, in adults ≥18 years presenting to primary care with acute sore throat, the use of a single dose of oral dexamethasone leads to increased speed of resolution or improvement in symptoms compared with placebo.

The trial has several secondary objectives. Firstly, to investigate whether dexamethasone compared with placebo leads to increased resolution or improvement in symptoms in those patients who have not been prescribed antibiotics. Secondly, to investigate whether dexamethasone compared to placebo will, in those patients offered a delayed antibiotic prescription, reduce the number of patients taking antibiotics for their sore throat within seven days. Thirdly, to investigate whether a single dose of oral dexamethasone compared to placebo will: reduce time away from work or education within seven days, not increase the incidence of hospital admission with complications related to sore throat (such as peritonsillar abscess) within 28 days, not increase repeat attendance at the GP within 28 days with symptoms or complications of sore throat, and be cost-effective. Fourthly, to assess predictors of response to corticosteroids including existing severity scores (FeverPAIN score and Centor score), baseline factors and positive bacterial throat swab.

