#### Secondary outcomes

The trial has several secondary outcomes which include: direct report by those patients who have not been prescribed antibiotics of presence or absence of complete resolution of sore throat at 24 hours by either text message or telephone, and report of presence or absence of complete resolution of sore throat at 48 hours by either text message or telephone contact. Additionally we will record for the seven days after treatment is administered: time to onset of pain relief (in hours), time to complete symptom resolution (in hours), report of difficulty swallowing and pain on swallowing, the duration of moderately bad symptoms recorded by validated symptom diary, the change in ratings of sore throat pain and pain on swallowing by visual analogue scale, the uptake of delayed antibiotic prescription and any time missed from work or education.

Furthermore we will record the severity of symptoms in the two to four days after seeing a GP based on the symptom diary, any attendance at GP practices, Emergency Departments, or out-of-hours centers within 28 days with symptoms or complications associated with sore throat such as peritonsillar abscess, any hospital admission with related complications of sore throat within 28 days, use of over-the-counter medications and prescription medications (including, if delayed antibiotics are taken, whether the course is completed and whether any other antibiotics were taken) in the first seven days and cost-effectiveness measures which include incremental cost, EuroQol EQ-5D-5L score change in seven days and impact on usual activities over most recent seven days

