#### Subsequent assessments

Following the baseline trial assessment participants complete a symptom diary reporting upon the resolution of symptoms and time to onset of pain relief, and rating their pain on a visual analogue scale every day for seven days on paper. As well as recording the severity and duration of their symptoms, this also includes providing information about NHS resource use, out-of-pocket expenditure, use of over-the-counter and prescription medications and time off work and/or education or foregone leisure time. Within the symptom diary we also ask participants to complete the EuroQol EQ-5D-5L instrument [20] daily for seven days following study entry.

Participants are telephoned or texted at 24 and 48 hours to support collection of the primary outcome and secondary outcomes. As preference this contact will be made via text message because of the greater accuracy with times and standardization. They are additionally telephoned in the first 96 hours if required to support and encourage completion of the symptom diary; they will also receive a text message at day four and day nine to encourage completion of the symptom diary and to remind them to return it to the PC-CTU. Follow-up is being undertaken by research coordinators at all three centers. Follow-up continues for seven days from the initial day of recruitment. Participants are asked to report in the diary any use of medications, including whether they obtained and completed the delayed antibiotic prescription. If participants do not complete the symptom diary over the seven days we send them a short questionnaire after this in order to collect information for key secondary outcomes relating to the first four days after taking the trial medication and, if needed, they are telephoned in order to help them complete the questionnaire. All paper diaries and questionnaires are sent back to the respective centre in pre-paid envelopes.

A review of the primary care notes is undertaken by the recruiting primary care site one month post-randomization, to record repeat presentation to a GP, Emergency Department or out–of-hours primary care centre with symptoms or complications of sore throat, hospital admissions and use of prescription medications. Baseline information about past medical history and acute and repeat medication usage is also collected.

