#### Inclusion in analysis

We will be analyzing our data using the intention-to-treat principle. All eligible randomized participants will be included in the analysis, assuming no complete resolution for missing data.

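### Times to pain relief and to complete resolution are to be compared as means by linear regression, although recording stops at seven days and the plan gives no value for participants still unresolved

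*Protocol article*

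**What the plan says.** The Secondary outcomes section defines the two times and their window: "Additionally we will record for the seven days after treatment is administered: time to onset of pain relief (in hours), time to complete symptom resolution", the latter also in hours. Subsequent assessments confirms where symptom follow-up ends: "Follow-up continues for seven days from the initial day of recruitment". The same section says that participants who do not complete the diary get a short questionnaire on the first four days.

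The section on statistical analysis for effectiveness and safety names both the summary and the model: "Mean and standard deviations for reported time to onset of pain relief, time to complete resolution of pain" will be calculated, with two further outcomes, and "compared between two treatment arms using a linear regression adjusting for antibiotic prescription". It then adds a general fallback, "All model assumptions will be assessed and if data do not conform to assumptions the alternatives will be explored", and refers the full methods to the statistical analysis plan.

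The only rule for absent outcome data that reaches the analysis set is under Inclusion in analysis: "All eligible randomized participants will be included in the analysis, assuming no complete resolution for missing data". The article does not mention censoring or a survival method, and assigns no time to a participant who has not resolved.

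**The concern.** A time in hours that is observed for at most seven days is right-censored at 168 h, or at the last diary entry if that comes sooner. Linear regression needs a completed value for each participant. Someone unresolved at day 7 must therefore be left out or given a value, and the article does not say which.

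The choice matters. Leaving them out selects on resolution by day 7, which treatment is meant to change, so the two groups of resolvers are no longer the groups that were randomised. The missing-data rule does not settle it: counting a participant as not resolved gives a yes/no value but no number of hours. The fallback clause does not settle it either. It depends on checks of model assumptions, and a regression fitted to resolvers alone can pass them because the censored participants are no longer in the data. The censoring is known from the design, so the method can be named now.

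At stake is the estimate, in hours, of the effect on the two times. They bear on the primary objective, which asks whether treatment "leads to increased speed of resolution or improvement in symptoms compared with placebo".

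**Working it through.** The article gives no figure for these two outcomes, so there is none to reproduce. The check compares what the regression would estimate under each way of handling unresolved participants.

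**Inputs from the article.** Window 7 × 24 = 168 h (Secondary outcomes; Subsequent assessments). Resolution at 24 h of 11% versus 29% (The number of participants).

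**Assumed inputs.** The proportion unresolved at day 7, the shape of the resolution curves and, for the exponential cases, a hazard ratio of 1.5.

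**Formulas.** Let S(t) be the proportion unresolved at time t and u = S(168).
- Restricted mean to 168 h: R = integral of S(t) from 0 to 168. With no earlier loss, this is the mean obtained when every unresolved participant is set to 168 h.
- Mean among resolvers: C = (R − 168u) / (1 − u).
- Exponential: rate λ = −ln(u)/168, and R = (1 − u)/λ.
- Weibull, S(t) = exp(−(t/s)^k), through the resolved proportions p24 and p168: k = ln[ln(1 − p168)/ln(1 − p24)] / ln 7, and s = 24 / [−ln(1 − p24)]^(1/k). R is then found numerically.

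**Example 1: exponential, hazard ratio 1.5, 20% of placebo unresolved.**
- Placebo: λ = −ln(0.20)/168 = 0.00958; R = 0.80/0.00958 = 83.5 h; C = (83.5 − 168 × 0.20)/0.80 = 62.4 h.
- Dexamethasone: λ = 0.01437; u = 0.20^1.5 = 0.0894; R = 0.9106/0.01437 = 63.4 h; C = (63.4 − 168 × 0.0894)/0.9106 = 53.1 h.
- Restricted mean difference 83.5 − 63.4 = 20.1 h. Resolvers-only difference 62.4 − 53.1 = 9.3 h.

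**Example 2: Weibull through 11% versus 29% at 24 h, 35% unresolved in both arms.**
- Placebo: k = 1.13, R = 107.5 h, C = (107.5 − 58.8)/0.65 = 74.9 h.
- Dexamethasone: k = 0.58, R = 89.4 h, C = (89.4 − 58.8)/0.65 = 47.1 h.
- Restricted mean difference 18.1 h. Resolvers-only difference 27.9 h before rounding. When u is equal in both arms, the resolvers-only difference is the restricted difference divided by 1 − u, so it is too large.

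**Range of cases** (differences in hours, from unrounded values):

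| Assumed curves | Unresolved at day 7, placebo vs dexamethasone | Restricted mean difference | Resolvers-only difference | Change |
|---|---|---|---|---|
| Weibull through 11% vs 29% at 24 h | 5% vs 2% | 24.3 | 21.8 | 10% lost |
| Same | 10% vs 5% | 25.7 | 22.1 | 14% lost |
| Same | 25% vs 15% | 28.4 | 22.6 | 20% lost |
| Same | 5% vs 5% | 18.4 | 19.4 | 5% too large |
| Same | 35% vs 35% | 18.1 | 27.9 | 54% too large |
| Exponential, hazard ratio 1.5 | 5% vs 1% | 16.3 | 11.8 | 28% lost |
| Same | 10% vs 3% | 18.6 | 11.1 | 40% lost |
| Same | 20% vs 9% | 20.1 | 9.3 | 54% lost |
| Same | 40% vs 25% | 18.7 | 6.0 | 68% lost |

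The effect shrinks in the cases where treatment leaves fewer unresolved at day 7. It is inflated where an early benefit has gone by day 7.

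**If unresolved participants are set to 168 h**, linear regression estimates the restricted mean difference without bias, provided nobody is lost earlier. That fails for a participant whose information ends before day 7, such as one who supplies only the four-day questionnaire: 168 h would then stand for a time that may have been shorter.

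**The case against.** The strongest reply is that the article does not say that anyone is dropped. It promises to analyse all eligible randomised participants, and it describes the times as recorded over seven days. A reader may take this to mean a value capped at 168 h, for which linear regression is sound. The article also commits to checking assumptions and leaves the full methods to an analysis plan that is not shown. This part stands: the documents show that the handling is unstated, not that the result will be biased.

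The size also depends on a day-7 rate and a curve shape that the article does not give. With few unresolved, the error can be 5% to 10%. It is probably smaller for onset of pain relief than for complete resolution.

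A reader might further infer that these are the only measures of speed, so that the primary objective is left without a sound analysis. The documents do not support that. Resolution at 24 h and at 48 h is binary and untouched. The planned area under the daily visual analogue scale curves also reflects speed and has values for participants who have not resolved.

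The reply does not remove the point. The article names the summary and the model, so this is more than a detail left open. An analysis plan that follows the sentence as written must still decide what to do with participants who have no time.

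**Conclusion.** The point holds in conditional form. The plan fixes means and linear regression for two times that are right-censored by design, and gives no value for unresolved or incompletely observed participants. If they are dropped, the assumed curves give anything from 10% lost or 5% too large to 68% lost or 54% too large, relative to the 7-day restricted mean difference. If they are set to 168 h, the result is a valid restricted mean when there is no earlier loss, and it should be labelled as one, because it is not a difference in mean time to resolution.

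A reader might go further and conclude that the planned estimate is certainly biased, or always towards no difference. Neither follows: the first depends on handling that the article does not state, and the second fails when both arms have the same proportion unresolved. Duration of moderately bad symptoms shares the sentence, but no calculation here covers it.

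The primary outcome, the 48 h outcome and the sample size do not change. This is a worthwhile correction to two secondary outcomes and ranks below a must-fix.

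**What to change.** For time to onset of pain relief and time to complete resolution, replace the linear-regression sentence with a time-to-event analysis:

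- Censor at the last diary entry or at 168 h, whichever comes first.
- Show Kaplan-Meier curves by arm.
- Report as the main estimate the difference in restricted mean time to 168 h, adjusted for antibiotic prescription, with its 95% confidence interval. The result stays in hours.
- Add in support a log-rank test stratified by antibiotic prescription, or a Cox model where proportional hazards is reasonable. Cox should not be the main model by default: in Example 2 the Weibull shapes differ by arm (1.13 versus 0.58), so hazards are not proportional.

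If linear regression is kept, state that unresolved participants are set to 168 h, call the result a 7-day restricted mean difference, and say how diaries that end early are handled.

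The cost is a few lines of wording and slightly different code, settled before unblinding. It needs no new data and no more participants.

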### Primary and secondary endpoints and outcome measures

#### Primary outcome

The primary outcome of this trial is the direct report by the patient of presence or absence of complete resolution of sore throat at 24 hours by either text message or telephone.

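### The daily pain scores are analysed only as a seven-day area without the baseline score, so no stated analysis estimates the size of pain reduction on day 1 or day 2

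*Protocol article*

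**What the plan says.** The primary objective (Objectives) is whether a single dose "leads to increased speed of resolution or improvement in symptoms compared with placebo". The primary outcome is "presence or absence of complete resolution of sore throat at 24 hours by either text message or telephone", and the 48-hour report has the same yes/no form.

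Graded pain is also recorded. Visual analogue scale (VAS) scores for throat soreness, pain on swallowing and difficulty swallowing are taken at baseline (Baseline assessments). Participants then keep a diary, "rating their pain on a visual analogue scale every day for seven days on paper" (Subsequent assessments). The Secondary outcomes section lists "the change in ratings of sore throat pain and pain on swallowing by visual analogue scale".

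The Statistics section turns these scores into one number per scale and participant: diary ratings by "visual analogue scale within seven days post-randomization to calculate areas under the curves as proxies for a summary measurement". Arms are compared on that number by linear regression adjusted for antibiotic prescription. Neither the baseline score nor centre is named as a covariate, although randomization is stratified by centre as well as by prescription.

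Other graded or timed outcomes exist. The Secondary outcomes section lists "time to onset of pain relief (in hours), time to complete symptom resolution (in hours"), duration of moderately bad symptoms, and diary severity in days two to four. The two times and the duration are compared between arms by adjusted linear regression.

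**The concern.** The Background expects the benefit of one dose to come early: more complete resolution at 24 hours, and onset of relief more than 6 hours sooner on average. A seven-day area weights the last days as heavily as the first, although sore throat usually settles in both arms. If the drug mainly lowers pain on the first two days, the area dilutes that effect.

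There is also a mismatch within the article. The listed outcome is a change in ratings. The stated analysis is the level of pain over the week with no baseline score in the model, so it neither measures change nor removes between-patient variation already present at entry.

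At stake is a clinically plain result: by how much pain fell on day 1 and day 2. The data for it are collected.

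**Working it through.** **1. The plan's own numbers.** The number of participants section gives 11% versus 29%, 90% power and 226 in total. With two-sided alpha 0.05 (assumed, as the article does not state it):
- Uncorrected: n' = [1.96 × √(2 × 0.20 × 0.80) + 1.2816 × √(0.11 × 0.89 + 0.29 × 0.71)]² / 0.18² = 101.7 per arm.
- With continuity correction: (n'/4) × [1 + √(1 + 4/(n' × 0.18))]² = 112.5, so 113 per arm, or 226.
- Doubled: 452. Allowing for loss: 452/0.80 = 565 (stated 566) and 452/0.85 = 532.

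The sample size reproduces and is not in dispute. The area regression uses all participants, so the relevant number is 452/2 = 226 per arm after loss. The no-antibiotic group has 113 per arm.

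**2. An assumed day-1 effect.** The documents give no VAS standard deviation. If the planned rates are read as a shift on a latent normal scale, d = z(0.29) − z(0.11) = −0.553 + 1.227 = 0.67 SD.

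**3. Effect retained by the area.** Treat the area as the mean of seven daily scores, with equal daily variance and equal between-day correlation ρ. Then:

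ratio to day-1 effect = mean(effect profile) / √((1 + 6ρ)/7)

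The denominator is 0.756 at ρ = 0.5 and 0.862 at ρ = 0.7. Power is for a two-sample t test, two-sided 0.05, with d = 0.67.

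| Effect profile | Mean of profile | Ratio (ρ 0.5 / 0.7) | Power, 226 per arm | Power, 113 per arm |
|---|---|---|---|---|
| Days 1-2 only | 0.286 | 0.378 / 0.331 | 77% / 66% | 48% / 39% |
| Halving daily | 0.283 | 0.375 / 0.329 | 76% / 65% | 47% / 38% |
| Falling by factor 0.7 daily | 0.437 | 0.578 / 0.507 | 98% / 95% | 83% / 72% |

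On the same assumption a day-1 contrast has at least 99.9% power at either size.

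**4. A smaller effect.** Take a constant 0.3 SD on the first k days, nothing after, ρ from 0.3 to 0.8 and 226 per arm. The area keeps 30-36% of the standardised effect on the early mean for k = 2, 44-49% for k = 3 and 58-62% for k = 4. For k = 2, power is 17-30% for the area and 92-98% for the days 1-2 mean.

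**5. When the dilution is slight.** Let the daily SD fall by 20% per day, with the effect on days 1-2 only.
- Day-2 effect held at 0.67 of its own, smaller SD: the ratio is 0.53-0.60 and power is 96-99% at 226 per arm.
- Day-2 effect held equal to day 1 in absolute units: the ratio is 0.58-0.66 and power is about 99%.

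**6. What the baseline score could add.** Suppose baseline correlates ρ with each day. Its squared correlation with the seven-day mean is ρ²/((1 + 6ρ)/7): 0.25/0.571 = 0.44 at ρ = 0.5 and 0.49/0.743 = 0.66 at ρ = 0.7. Dividing the standardised effects from the first two rows of step 3 (0.25 and 0.22) by √(1 − 0.44) = 0.75 or √(1 − 0.66) = 0.58 gives 0.34 and 0.38, or 95-98% power at 226 per arm. This is a favourable case, since correlation with baseline is likely to weaken over the week.

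**The case against.** The strongest reply has four parts.

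- **Early benefit is covered elsewhere.** A reader might infer that it is tested only as resolved or not at 24 and 48 hours, and that the improvement part of the objective goes unanswered. The article does not support this. Time to onset of pain relief credits early, partial relief and is compared between arms. Time to resolution and duration of moderately bad symptoms are also compared, and severity in days two to four is a listed outcome. This stands. What these outcomes do not give is the amount of pain reduction on day 1 or day 2. Onset says when relief starts, the next two depend on thresholds, and days two to four leave out day 1.
- **The detail belongs to the statistical analysis plan.** Full methods are deferred to it, and silence on the days two to four analysis is no finding. But the article does state a method for the VAS scores, and that stated method is what is questioned here.
- **An area per participant is a standard summary.** It avoids seven daily comparisons. This is true, and it is why the seven-day average should be kept.
- **The power loss rests on assumptions.** This stands. The area is analysed in all participants, so 226 per arm is the fair basis and not 113. Steps 3 and 5 also show cases where little is lost.

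A reader might also compare the power of the yes/no primary outcome with that of a pain score. That has no bearing here, because the primary outcome is not proposed for change.

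**Conclusion.** The point holds in a limited form. The stated VAS analysis does not match the listed outcome of change in ratings. It leaves out a baseline score that is collected, and it yields no estimate of pain reduction on the two days when the rationale places the benefit.

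How much this costs is uncertain. With equal daily variance and a short-lived effect, the area keeps about 0.33-0.38 of the day-1 standardised effect, and power is 65-77% at 226 per arm for a 0.67 SD day-1 effect. With slower decay it is 95-98%, and with shrinking daily spread 96-99%. The documents give no VAS SD, correlation or time course, so none of these cases can be preferred. It would be too strong to say that the area averages the effect away. The primary outcome and the sample size are not affected.

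**What to change.** In the Statistics section and the statistical analysis plan:

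1. Leave the 24-hour primary outcome and the sample size as they are.
2. Replace the area regression by a repeated-measures model of the daily VAS scores with baseline score, centre, prescription stratum, day, arm and arm-by-day.
3. Name the day-1 and day-2 throat-soreness contrasts as secondary analyses.
4. Derive the seven-day average (the area) from the same model, so the planned summary is still reported.

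At minimum, keep the area regression and add the baseline VAS score and centre as covariates. That may recover much of the precision (step 6) but still gives no day-1 or day-2 estimate.

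The cost is one model in place of another on data already collected. The model can also use incomplete diaries, if missing entries are taken as missing at random given the observed scores. The downside is one or two more named secondary contrasts. They rely on return of the paper diary and on when the day-1 entry is filled in, so the plan should state the intended time of that entry.
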